**STAFF**					
Distress associated with difficult behaviour for people with cognitive impairment	Residents’ Challenging Behaviour related Distress Index	The Residents’ Challenging Behaviour related Distress Index includes 10 items that address altered behaviour such as hallucinations, instability, anxiety, depression, apathy, euphoria, limited communication skills, disinhibition, aggression, and impaired motor skills. All items are rated in terms of the degree of distress 1 = does not stress me at all, 2 = stresses me somewhat, and 3 = stresses me a lot. The score ranges from 0—100 points, with a higher score indicating higher distress [60]	Self-rating by staff	t_0_, t_7_	Secondary outcome
Person-centred care	Person-Centred Practice Inventory – Staff (PCPI-S)	The Person-Centred Practice Inventory—Staff includes 59 items covering 17 different constructs of person-centredness with respect to 3 domains: prerequisites, care environment, and person-centred processes. The items are measured on a 5-point Likert scale from 0 = strongly disagree to 4 = strongly agree. Overall, the scale shows a sum score of 0—100, with higher scores representing greater agreement with person-centredness [61, 62]	Self-rating by staff	t_0_, t_7_	Secondary outcome
Sociodemografic variables	Single items	• Age in years • Gender	Self-rating by staff	t_0_, t_7_	Secondary outcome

^a^t_0_ = before implementation of intervention; t_1_ = admission; t_2_ = day 3 of hospital stay; t_3_ = day 7 of hospital stay; t_4_ = day 14 of hospital stay; t_5_ = discharge from the ward; t_6_ = 30 days after discharge; t_7_ = 6 months after baseline

^b^With Outcome-oriented nursing assessment AcuteCare (epa-AC ©) the patient's abilities and impairments are assessed daily by registered nurses using the four-level epa point system and recorded in electronic form [50]

##### Patient level

At patient level, we will collect data at a maximum of six timepoints: t_1_ (at admission), t_2_ (at day 3), t_3_ (at day 7), t_4_ (at day 14), t_5_ (at discharge), and t_6_ (30 days after discharge). We will collect study documentation data (e.g., participant flow) paper-based and outcome data electronically using REDCap®. Trained study staff will accompany people with cognitive impairment for self-rating. Proxy-rating will be carried out by trained study staff or nurses who have been responsible for the participant for at least one shift within the past 24 h. In case of non-participation of people with cognitive impairment in the study, we will document the reason.

Data at patient level will be documented using participant codes. We will keep identification lists and paper-based documents under lock, separate from other study material and only accessible to data collectors. Electronic data will be password-protected and only accessible to the research team. We will automatically carry out a complete backup of the data every day. With the set-up of the database, we have stored definitions (e.g., minimum and maximum) for each value to be entered, which minimises the entry of invalid data. In addition, the biostatistician will perform quality and plausibility checks (data validation).

##### Staff level

For outcomes at staff level, we will use a paper-based questionnaire at two timepoints: t_0_ (before intervention phase) and t_7_ (after six months). We will collect the data pseudonymously and use a self-generated code to allow both sets of data of one participant to be matched over the course of the study. To increase retention, we will use incentives and email reminder to ward managers.

Only data collectors will have access to the paper-based questionnaires, which are kept under lock. We will keep potentially identifying data separate from the rest of the study material. One person will conduct electronic data entry and random samples of the record will be double-checked by another person. In case of discrepancies, the entire data entry will be double-checked.

#### Assignment of intervention

Allocation of wards as intervention or control ward was based on ward managers’ decision to participate in the intervention. Participants’ assignment will be determined by their wards’ assignment.

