## Objectives

This study aims to test the feasibility and clinical effectiveness of the newly developed PCC intervention. Therefore, our objectives are to assess (a) initial effects, (b) the degree and quality of implementation, mechanisms of change and contextual factors, and (c) potential cost savings of the intervention.

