##### Cluster level

We will purposefully select six peripheral wards with a prevalence of at least 30 people with cognitive impairment per month according to data from hospital controlling. We will exclude intensive care, intermediate care, psychiatric, palliative, and paediatric wards. Based on the recommendation of nursing management, we will identify eligible wards and recruit them through individual information meetings with ward managers.

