#### Sample size

The sample size is based on a recent retrospective cohort study which investigates the length of hospital stay in older people living with dementia by matching people without dementia in Germany [63]. We assume a mean reduction in the length of hospital stay of three days (intervention vs. control). With a standard deviation of 18 vs. 16 days, an intraclass correlation coefficient of 0.05 [64], and three clusters per treatment group with 120 people with cognitive impairment each, the adjusted two-sample t-test will reach a power of 81.5% at one-sided significance level of 50% [65]. Thus, this exploratory trial will be sufficiently powered to show the hypothesized direction of effect only.

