#### Data collection and management

We will use claims data from the hospital to determine the potential cost savings of the intervention. These will be available at the hospital controlling department. This data includes Diagnosis Related Groups (DRG) charges, length of hospital stay, cost weight, gender, and primary and secondary International Statistical Classification of Diseases and Related Health Problems (ICD) diagnoses. The data will be delivered pseudonymously to the evaluators via a secure data exchange platform. In addition, we will collect training costs consisting of salaries of the nursing staff, the costs of the lecturers as well as material costs for premises, catering and travel costs.

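### Wards chose their own arm and stay is compared only after the start: on the plan's ICC, ward differences alone give the contrast an SD of 3.1 days against a 3-day target, with no baseline-adjusted ward analysis

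*Protocol article*

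**What the plan says.** **Allocation.** Under Assignment of intervention: "Allocation of wards as intervention or control ward was based on ward" managers' choice to join the intervention. The next sentence reads "Participants’ assignment will be determined by their wards’ assignment", so ward is nested in arm.

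**Period compared.** Patients are recruited over six months, and Table 1 reads length of stay at t5 (discharge) for those patients. No pre-intervention stay enters the primary or the economic analysis. The t0 and t7 measures are staff questionnaires. The one t0 ward item on stay is a minimum for special wards, reported by ward managers.

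**Adjustment.** The Data analysis section (evaluation of effects) plans a stratified log-rank test and a propensity score. The score uses age, gender, severity of cognitive impairment, comorbidity, admission type, recent hospitalisations, and either the DRG-related or the ward-related expected stay. Clusters are to be handled at least as fixed effects.

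**Sample size.** "We assume a mean reduction in the length of hospital stay of three days (intervention vs. control"). The cluster-adjusted t-test "will reach a power of 81.5% at one-sided significance level of 50" per cent. The section adds that the trial is powered for the direction of effect only.

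**Objective.** "This study aims to test the feasibility and clinical effectiveness of the newly developed PCC intervention". The following sentence lists initial effects among the aims.

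**Routine data.** Wards are selected on the number of people with cognitive impairment "per month according to data from hospital controlling". The economic evaluation will use claims data that include length of stay and ICD diagnoses: "These will be available at the hospital controlling department". The Setting section cites a 2022 count from the same source.

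**The concern.** Stay on a ward depends on more than its patients. Rounds, discharge routines, staffing and links to follow-on care all matter, and a manager who volunteers for a new nursing role may already run a different ward. With three self-selected wards per arm and no look at how they differed beforehand, such differences cannot be told apart from the intervention.

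The planned fixed ward effects do not help. Six ward effects already determine the arm indicator, so an arm effect cannot be estimated beside them. If ward were the stratification factor in the log-rank test, each stratum would hold one arm only and contribute nothing.

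The stake is the trial's one quantitative claim. The article limits itself to direction, and direction is what a standing ward difference can decide.

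**Working it through.** **Inputs** (Sample size section): difference 3 days; SDs 18 and 16; ICC 0.05; three wards per arm; 120 patients per ward. Everything below is on the scale of the t-test used for planning, not of the log-rank test.

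**1. The plan's own figure.** Pooled variance = (18² + 16²)/2 = 290, SD 17.03. Design effect = 1 + 119 × 0.05 = 6.95. SE = √(290 × 2 × 6.95/360) = 3.346 days. At one-sided 50% the critical value is 0, so power = Φ(3/3.346) = 0.815. The stated 81.5% reproduces.

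**2. Part due to wards.** Between-ward variance = 0.05 × 290 = 14.5, so ward SD = 3.81 days. For the difference between two 3-ward means, SD = 3.81 × √(2/3) = 3.11 days. The patient part is √(275.5 × 2/360) = 1.24 days. Wards supply 3.11²/3.346² = 86% of the variance, and more patients per ward cannot reduce that part.

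With no effect and wards assigned at random, the ward part alone would reach 3 days in either direction with probability 33.5%, and in the intervention's favour with probability 16.7%. The 3.11 moves with the ICC: 1.39 days at 0.01, 1.97 at 0.02, 2.41 at 0.03, 4.40 at 0.10.

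**3. What self-selection adds.** Step 1 treats ward differences as mean-zero noise. Suppose instead that, with no intervention effect, the volunteer wards had a systematic advantage of b days (assumed values). The chance of the expected sign is Φ(b/3.346): 50% at b = 0, 61.7% at 1, 72.5% at 2, 81.5% at 3. A disadvantage of 3 days would pull the stated 81.5% down to 50%. The article does not show the sign or size of b.

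**4. What a baseline period could do.** Let m be patients per ward in each period and r the correlation of a ward's effect between periods. Both are assumptions.

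Difference-in-differences: variance = (2/3) × [2 × 14.5 × (1 − r) + 2 × 275.5/m].

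Ward-level ANCOVA with the slope taken as known: variance = (2/3) × [v − (14.5r)²/v], where v = 14.5 + 275.5/m.

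| r | Diff-in-diff SE, m = 120 | ANCOVA SE, m = 120 | Diff-in-diff SE, m = 60 |
|---|---|---|---|
| 0.3 | 4.07 | 3.23 | 4.43 |
| 0.5 | 3.57 | 3.02 | 3.97 |
| 0.7 | 2.98 | 2.67 | 3.45 |
| 0.8 | 2.63 | 2.42 | 3.16 |
| 0.9 | 2.23 | 2.11 | 2.84 |

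The reference is the current 3.35. At m = 120, differencing gives Φ(3/SE) of 80%, 84%, 87% and 91% for r = 0.5, 0.7, 0.8 and 0.9. At m = 60 it gives 81%, 83% and 86% for r = 0.7, 0.8 and 0.9.

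Break-even for differencing: set 29(1 − r) + 551/m equal to 14.5 + 275.5/120 = 16.80. This gives r = 0.58 at m = 120 and r = 0.74 at m = 60. At m = 30 the patient term alone is 18.37, so no r reaches break-even.

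**The case against.** Much of this is disclosed. The trial is labelled exploratory and placed at the feasibility stage. The Discussion concedes the risk of selection bias and promises to consider baseline differences. The Sample size section claims direction only. A request to print power at a conventional level beside the 81.5% (18.6% at one-sided 5%: noncentral t, 4 df, noncentrality 3/3.346 = 0.897) would be a matter of taste. This stands, but admitting a bias does not measure it, and the promised adjustment covers mainly patient mix.

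Three stronger readings are tempting, and the article does not support them.

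- *The propensity score ignores wards.* It includes DRG-expected or ward-related stay, and Table 1 defines the latter as a ward minimum. A mandated minimum stay is therefore a planned covariate, and DRG stay picks up part of the specialty mix.
- *Any result in the right direction will count as success.* A reader might infer this from the 50% level, but no success rule is stated.
- *The baseline data exist and are ignored.* That controlling can supply previous-year stay by ward is an inference from the Setting, Cluster level and economic sections. No sentence says so.

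The objections to the remedy also stand. The Background says formal diagnoses are often missing, and patients merely at risk of delirium are enrolled, so a coded subset may fall well below 120 per ward. Its size cannot be read from the article: about 1,500 diagnosed inpatients a year hospital-wide is 125 a month, while six wards with at least 30 each imply 180. Screening by the expanded practice nurses could raise coding on intervention wards only, and differencing would read the changed case mix as an effect. Differencing also needs parallel trends.

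**Conclusion.** The concern holds as a weakness that should be addressed. It does not invalidate the design. On the plan's own ICC and SDs, the expected ward-only SD of the arm contrast (3.11 days) is about the size of the target effect (3 days), and neither the propensity score nor nested ward effects can remove what is specific to a self-selected ward. The 81.5% is arithmetically right but conditional on ward differences averaging zero.

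The 3.11 days is one standard deviation under an assumed, unadjusted ICC, not an observed gap. Covariate adjustment may lower it, and at ICC 0.02 it is 1.97. Whether ward differences are stable over time is also assumed. A reader might therefore go on to make difference-in-differences the main estimate. The numbers do not support that step, because precision worsens below a correlation of about 0.58 (120 per ward) or 0.74 (60 per ward) and the article gives no such correlation. The case for baseline data rests on exposing, and partly removing, standing ward differences, not on a promised gain in precision.

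**What to change.** 1. Ask hospital controlling whether it can supply length of stay for patients aged 65 and over with coded cognitive impairment on the same six wards, for the same calendar months of the previous year.
2. Keep the planned primary analysis. Add a pre-specified supplementary ward-level analysis adjusted for baseline stay, with its confidence interval and the same coded case definition in both periods. Choose between ANCOVA and difference-in-differences in advance. ANCOVA is more precise on the figures above, but with six wards its slope is poorly estimated, and in self-selected groups it removes standing differences only in part. Differencing removes stable differences but needs parallel trends.
3. Report coded cases per ward and period, so that a change in coding on intervention wards is visible, and read the direction claim in the light of this analysis.
4. Reword the Objectives so that the trial estimates the direction and size of initial effects, in line with the Sample size section.

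The cost is one more pseudonymised extract and some wording; no further patients are needed. The drawbacks are a smaller coded sample, precision that depends on an unknown correlation, and reliance on parallel trends and stable coding.

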#### Blinding

Due to the nature of the intervention, blinding of participants, EPN providing the intervention, and researchers collecting data is not feasible. However, we will blind the biostatistician during data analyses regarding group allocation of clusters (neutral group IDs) and participating people with cognitive impairment.

#### Sample size

The sample size is based on a recent retrospective cohort study which investigates the length of hospital stay in older people living with dementia by matching people without dementia in Germany [63]. We assume a mean reduction in the length of hospital stay of three days (intervention vs. control). With a standard deviation of 18 vs. 16 days, an intraclass correlation coefficient of 0.05 [64], and three clusters per treatment group with 120 people with cognitive impairment each, the adjusted two-sample t-test will reach a power of 81.5% at one-sided significance level of 50% [65]. Thus, this exploratory trial will be sufficiently powered to show the hypothesized direction of effect only.

#### Data analysis

Statistical analysis is according to intention-to-treat (no exclusions). We will evaluate the primary outcome length of hospital stay by the stratified log-rank test (death is censored). Nota bene, the stratified log-rank test has very similar characteristics as the stratified van-Elteren rank-sum test and is available in many (statistical) software packages. We will use a propensity score approach (PSA) to balance individual characteristics between participants in intervention and control groups. In the multivariable logistic regression for PSA, we will use the independent variables age, gender, severity of cognitive impairment, Charlson Comorbidity Index, admission type, expected admission diagnosis-related or ward-related length of stay, and hospitalisations during the last 7 days [66, 67] as these variables are likely to be associated with outcome. Moreover, we will carefully monitor mortality in both arms, although we do not expect any difference. We will evaluate secondary outcome measures by (generalised) mixed models for repeated measures over time. If feasible, we will take outcome measures (particularly those reported by people with cognitive impairment) over the course of hospital stay. Thus, we may need to evaluate the outcome trajectories by random coefficient models. We will categorise and compare safety outcomes by frequency, relatedness, seriousness, and severity. Moreover, we will summarise variables by mean, standard deviation, and percentiles (0, 25, 50, 75, and 100) respectively by absolute and relative frequencies (percentage). Due to the small number of clusters, we will at least account for them in a fixed effect analysis. Though we will attempt to estimate corresponding random effects (e.g., to derive intraclass correlation), this seems prone to bias.

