**PEOPLE WITH COGNITIVE IMPAIRMENT**					
Length of hospital stay	Single item	Number of days people with cognitive impairment stayed in hospital during a single admission event [34]	Patient records	t_5_	Primary outcome
Prevalence of delirium	Confusion Assessment Method – short form (CAM)	The Confusion Assessment Method consists of 4 items on (1) acute onset and/or fluctuating course, (2) inattention, (3) disorganised thinking, and (4) altered level of consciousness. Delirium is indicated sensitively if item (1) and (2), and either (3) or (4) are scored positive [35–37]	Rating by research team	t_1_, t_2_, t_3_, t_4_, t_5_	Secondary outcome
Severity of delirium	Confusion Assessment Method – Severity (CAM-S)	Delirium severity is measured using the Confusion Assessment Method by rating the items in terms of severity (0 = absent, 1 = mild, 2 = marked). The item (1) acute onset and/or fluctuating course is only rated as 0 = absent or 1 = present. Overall, the scale ranges from 0—7 points, with higher values indicating a more severe degree [38]	Rating by research team	t_1_, t_2_, t_3_, t_4_, t_5_	Secondary outcome
Delirium subtype	Delirium Motor Subtype Scale (DMSS)	The Delirium Motor Subtype Scale consists of two subscales on hyperactive (4 items) and hypoactive (7 items) subtype, classifying four different motor subtypes: hypoactive, hyperactive, mixed or no motor subtype. Each item is scored dichotomously (present or absent) over the past 24 h. Hyperactive delirium is positive, when two items on the hyperactive subscale are present. Hypoactive delirium is positive, when either “decreased amount of activity” or “decreased speed of actions” in combination with at least one other item is present. Mixed type is positive, when both hyper- and hypoactive delirium was positive within the last 24 h [39, 40]	Rating by registered nurses	t_1_, t_2_, t_3_, t_4_, t_5_	Secondary outcome
Prevalence of pain	Numeric Rating Scale (NRS)	The Numeric Rating Scale is a 11-point scale ranging from 0 (no pain) to 10 (worst possible pain) [41]. A value ≥ 1 indicates pain	Self-rating by people with cognitive impairment	t_1_, t_2_, t_3_, t_4_, t_5_	Secondary outcome

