Person-centred care	Individualised Care Scale (ICS)	The Individualised Care Scale consists of 17 items measuring the perspective of people with cognitive impairment on implementation of individualised care during hospitalisation. Items are rated with a 5-point Likert scale ranging from 1 = strongly disagree to 5 = strongly agree. A general score is calculated as mean value between 1 and 5, with higher values indicating more individualised care [55, 56]	Self-rating by people with cognitive impairment	t_5_	Secondary outcome
Falls	Single items	Number of falls documented	Patient records	t_5_	Secondary outcome (safety outcome)
Physical restraints	Single items	Occurrence of the use of physical restraints	Retrospective rating by registered nurses	t_2_, t_3_, t_4_, t_5_	Secondary outcome (safety outcome)
Prescription of antipsychotics	Predefined list	Newly prescribed antipsychotic medication during hospitalisation	Patient records	t_5_	Secondary outcome (safety outcome)
Mortality	Single items	People with cognitive impairment that died during data collection	Patient records	t_6_	Secondary outcome (safety outcome)
Stability of care arrangements	Single items	• Number of readmissions within 30 days • Perceived stability of care arrangement	Telephone interview with people with cognitive impairment and/or their relatives	t_6_	Secondary outcome (safety outcome)
Sociodemographic variables	Single items	• Age in years • Gender: Male, female, or divers • Care dependency levels ranging from 1 to 5 • Care situation before admission	Patient records	t_1_	Control variable
Admission diagnosis	Single items	Admission diagnosis as documented	Patient records	t_5_	Control variable
Type of admission	Single items	Emergency or planned admission	Patient records	t_1_	Control variable
Previous hospital admissions	Single items	Number of hospital admissions within the last seven days	People with cognitive impairment and/or their relatives	t_1_	Control variable
Admission diagnosis-related (diagnosis related groups) length of hospital stay	Single items	Mean stated length of stay of the patient's diagnosis-related group	Patient records	t_5_	Control variable
Or Ward-related length of hospital stay		Minimum length of stay of special wards, e.g., based on rehabilitation programmes	Ward managers	t_0_	
Type of discharge	Single items	Discharge home, transfer	Patient records	t_5_	Control variable

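### Censoring in-hospital deaths in the primary log-rank test compares discharge rates among patients still alive in hospital; the sign for length of stay needs a companion analysis that treats death as a competing event

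*Protocol article*

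**What the plan says.** Table 1 of the protocol article defines the primary outcome as "Number of days people with cognitive impairment stayed in hospital during a single admission event". The Data analysis section under Evaluation of effects fixes the test: "We will evaluate the primary outcome length of hospital stay by the stratified log-rank test (death is censored". On deaths it adds only this: "Moreover, we will carefully monitor mortality in both arms, although we do not expect any difference". Mortality is a separate safety outcome in Table 1, collected at t6 (30 days after discharge) and described as "People with cognitive impairment that died during data collection".

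The Sample size section plans a cluster-adjusted t-test at a one-sided level of 50% and concludes that "this exploratory trial will be sufficiently powered to show the hypothesized direction of effect only". Under Assignment of intervention, wards joined an arm by their managers' decision and were not randomised. The Background attributes both longer stays and higher mortality to the same set of adverse events, and it hypothesises that the intervention shortens stay by reducing those events.

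**The concern.** A patient who dies in hospital can no longer be discharged alive, so death competes with the event being analysed. Censoring at death takes that patient out of the risk set. The log-rank test then compares discharge rates among those who remain alive in hospital. Reading its sign as a statement about length of stay requires more: either equal mortality in both arms, or deaths unrelated to how long the patient would otherwise have stayed.

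The article secures neither. Equal mortality is an expectation, in wards that chose their arm. On the second condition, the Background's account of adverse events points towards long stayers being the ones who die. In that case the arm with more deaths loses slow patients from its risk set and can look faster, and an arm with fewer deaths can look slower.

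The sign is at stake. A one-sided 50% level has no significance margin to absorb even a small shift.

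**Working it through.** **1. The plan's own figure.** Inputs from Sample size: a mean stay three days shorter under the intervention; SDs of 18 and 16 days; ICC 0.05; three wards of 120 per arm, so 360 per arm.
- Design effect = 1 + (120 − 1) × 0.05 = 6.95.
- SE = √[(18² + 16²)/360 × 6.95] = √(1.611 × 6.95) = 3.346 days.
- Power at one-sided 50% = Φ(3/3.346 − 0) = Φ(0.897) = 81.5%.

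This reproduces the stated 81.5%. It confirms that the criterion is simply whether the observed difference has the hypothesised sign.

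**2. How the shift arises.** At each discharge time j the log-rank score adds d₁ⱼ − dⱼ·n₁ⱼ/nⱼ, where n counts patients alive and still in hospital. A death lowers n₁ⱼ at all later times. If the patient removed would have been discharged slowly, those left are faster on average and the score moves towards that arm. If the patient removed was typical of those remaining, nothing moves on average.

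**3. Size under assumed inputs.** None of the following is in the documents: lognormal stay with mean 15 and SD 17 days; in-hospital deaths 5% in one arm and 10% in the other; correlation ρ between would-be stay and latent death time (negative means would-be long stayers die). There is no true difference in stay, 360 patients per arm, and 500 simulated trials per scenario, using the unstratified log-rank test. The percentages are trials in which the higher-mortality arm looks faster.

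| Dependence | Mean Z, death censored | Censored, no ward effect | Censored, ICC 0.05 | Deaths as never discharged alive, ICC 0.05 |
|---|---|---|---|---|
| None (ρ = 0) | −0.06 | 48% | 49% | 22% |
| Moderate (ρ = −0.4) | 0.28 | 62% | 56% | 27% |
| Strong (ρ = −0.8) | 0.80 | 80% | 65% | 32% |
| Opposite (ρ = +0.4) | −0.31 | 36% | 47% | 22% |

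The Monte Carlo standard error near 50% is √(0.25/500) = 2.2 percentage points. The clustered 49% and 47% are therefore not distinguishable from 50% on their own; the opposite shift shows clearly only without ward effects (36%).

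**4. Cross-check of the clustered column.** Dividing mean Z by √6.95 = 2.636 gives Φ(−0.023) = 49%, Φ(0.106) = 54%, Φ(0.303) = 62% and Φ(−0.118) = 45%. These are close to the simulated 49%, 56%, 65% and 47%.

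**5. Other mortality contrasts, ICC 0.05, death censored.** At 5% vs 8%: 50% (moderate) and 62% (strong). At 5% vs 15%: 58% and 71%. With no dependence, even 5% vs 15% gives 53%.

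**6. If the higher-mortality arm truly lengthens stay.** Mean Z without ward effects, where a positive value means the wrong sign on average:
- +0.5 day, 5% vs 10%: −0.24 (moderate), +0.28 (strong).
- +0.5 day, 5% vs 15%: −0.02 (moderate), +0.89 (strong).
- +1 day, 5% vs 10%: −0.35 (strong).
- +1 day, 5% vs 15%: −0.43 (moderate), +0.32 (strong).
- +3 days, 5% vs 15%: −1.88 (strong).

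**The case against.** The case for leaving the plan alone has real force. A log-rank test with deaths censored is a valid test of equal cause-specific discharge rates. A misleading sign for stay needs a mortality difference and dependence between death and would-be stay, and the article quantifies neither. Mortality is monitored and compared, so an excess of deaths would be seen. The propensity score includes age, comorbidity, severity of cognitive impairment, admission type and expected stay, which could absorb part of the dependence. Ward clustering dilutes the shift, as the table shows. Supportive analyses may stand in a statistical analysis plan that is not shown.

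Most of this limits the size of the point without removing it. The article itself fixes the handling of death and does not tie the mortality comparison to the conclusion on stay.

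Three stronger readings are tempting and not supported:
- A reader might infer that censoring reverses the direction of effect. On average that appeared only with strong dependence, doubled or tripled mortality and a true lengthening of one day or less. A true lengthening of three days, the size of the planned effect, never reversed on average.
- A reader might take the last column of the table as the correct answer and its distance from the censored column as bias. It answers a different question, combining stay with survival.
- Table 1 files type of discharge ("Discharge home, transfer") as a control variable although it is recorded at discharge. One might infer that this distorts the primary test. It is not among the listed propensity variables and no adjustment for it is stated, so no effect on the test is shown.

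**Conclusion.** The point holds conditionally. The primary test as described answers a narrower question than which arm leaves hospital alive sooner, and the trial's single conclusion is the sign of that answer. Suppose deaths are 5% vs 10%, there is no true effect and the ICC is 0.05. The censored test then favours the higher-mortality arm in about 56% to 65% of trials if would-be long stayers are the ones who die, about 49% if deaths are independent, and about 47% under the opposite dependence. These figures are an illustrative range and not an estimate for this trial: mean stay, mortality and dependence are assumed, and neither the stratification nor the propensity score was modelled. The documents do not show that the result will be biased, or in which direction. They do leave the reading of the sign resting on equal mortality in wards that chose their arm.

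**What to change.** Keep the stratified log-rank test and describe it as a cause-specific comparison of discharge rates. Prespecify one companion analysis of discharge alive with death as a competing event: Gray's test on the cumulative incidence, or a rank analysis with deaths placed as the longest stay. Plot cumulative incidence of discharge alive instead of Kaplan-Meier curves. State that the direction of effect will be interpreted together with this analysis and with in-hospital deaths by arm, counted separately from deaths after discharge. A rule that both analyses must agree before a shorter stay is claimed is one option, but that is a matter of preference.

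The cost is analysis-plan wording and a few lines of code, with no new data. The downside is one more primary-outcome analysis to report, and it mixes stay with survival, so its meaning has to be explained beside the log-rank result.
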